### Study drugs and devices

In accordance with the Medicines for Human Use (Clinical Trials) Regulations 2004 and Directive 2001/20/EC, the drugs under investigation in this trial fall under the definition of ‘investigational medicinal product’ (IMP). Although the insulins used during this trial fall under the definition of IMPs they will be used under existing licence.

### Insulin for MDI participants

For the participants randomised to MDI, insulin aspart will be given as 3 ml cartridge 100 Units/mL in a pre-filled pen (*Flexpen®*). Insulin glargine will be given as 3 ml cartridge 100 Units/mL in a pre-filled pen (*SoloStar®*). However, for those participants who have had a previous negative experience or adverse effect with insulin aspart, insulin lispro will be offered as 3 ml cartridge 100 Units/mL in a pre-filled pen (*Kwikpen®*).

### Insulin for CSII participants

For participants randomised to CSII, insulin aspart will be the insulin used as 10 ml vial 100 Units/mL. Insulin lispro can be used instead of insulin aspart for those who have had previous negative experience / adverse effects.

### Insulin pumps

All participants will be given an insulin pump that can receive and display CGM data (Mini-Med Paradigm Veo insulin pump) and will be taught how to use the on-board bolus calculator. Only those randomised to CSII will use the pump for insulin administration, the MDI groups will only use the bolus calculator feature and, if randomised to RT-CGM, the CGM feature. All participants randomised to CSII (insulin pump therapy) will be given a single additional session restricted to technical aspects of pump management.

### Self Monitoring of Blood Glucose (SMBG)

All participants will be required to undertake daily 4-point and weekly 8-point self-monitored capillary glucose profiles. All participants will use the Contour link®, Bayer Healthcare meter and will undertake this whether or not concurrent RT-CGM is being used.

### Real time—continuous glucose monitoring

Fifty per cent of all participants will be randomised to real time monitoring, using the CE-marked REAL time continuous glucose monitor (Medtronic).

### Advice on interpretation and action from SMBG / RTCGM

All participants will attend an education session on the recording of SMBG but, for those participants randomised to RT-CGM, this session will also include the technical aspects of using the monitor. This includes trend analysis, hypoglycaemia and hyperglycaemia alarms. Participants will be given written instructions on how to use the data provided by continuous glucose monitors to make real-time adjustments of insulin doses and on the use of computer software (for those with a home computer) to retrospectively review the glucose data to alter future insulin doses. Participants randomised to RT-CGM will be encouraged to wear the sensor continuously but flexibly with a minimum of 7 days continuous monitoring in the final week of each month. Those participants randomised to RT-CGM will be advised to re-site the sensor every 7 days.

### Blinded continuous glucose monitors

Blinded CGM will be undertaken using the CE-marked Medtronic wireless iPro system. These will be used in the 4-week wash in period and during the last seven days of every month. The patients and investigators are blinded to all of this data until the end of the primary 24 week RCT.

### Insulin titration protocol

The blood glucose targets (for all patients in CSII and MDI groups) will be as follows:

Fasting blood glucose (FBG): 5.0 - 7.0 mmol/l.

Pre-prandial blood glucose: 4.5 - 7.0 mmol/l.

Post-prandial glucose*: 6.0 – 8.0 mmol/l.

Bedtime blood glucose**: 6.0 – 8.0 mmol/l.

4 am blood glucose: 5.0 – 7.0 mmol/l.

*postprandial blood glucose: measurement made 2 h after the start of a meal.

**bedtime blood glucose: measurement made within 30 min of retiring to bed for the night.

### Glargine titration in MDI group

Insulin glargine will be self-administered and the following titration protocol will be followed:

Take within 30 min of retiring to bed for night / no need for snack.

Aim for stable (not falling) glucose through the night.

Reduce dose if any hypoglycaemic episodes or glucose <5.0 mmol/l between 4 am and before breakfast.

Target glucose of 5–7 mmol/l before breakfast—adjust dose by 1–2 units to maintain target if necessary with primary aim being absolute avoidance of BH (Biochemical Hypoglycaemia).

During periods of illness, basal insulin doses may need to be altered and this will be guided by SMBG levels.

### Introduction of twice daily glargine

Participants randomised to MDI already on twice daily glargine will continue on this from the outset of the RCT. In other MDI participants, if glucose is consistently >7 mmol/l before evening meal or highly variable between breakfast and evening meal, add second dose of insulin glargine before breakfast. Initial dose will be 4 units but can be adjusted in light of participant’s current insulin doses. If glucose has been falling through the night, a 2–4 unit reduction in evening glargine dose will be actioned before bed on the day of commencing the morning dose. The addition of a second daily glargine dose will be considered for all participants in the MDI group. This can be initiated between study visits if necessary, e.g. after telephone advice.

Morning insulin glargine will be self-administered and adjusted as follows:

Take within 30 min of rising from bed for the morning.

Aim for stable (not falling) glucose through the afternoon.

Reduce dose if any hypoglycaemic episodes or glucose <5 mmol/l between 2 h after lunch and evening meal.

Target glucose of 5-7 mmol/l before evening meal – adjust dose by 1–2 units to maintain target if necessary with primary aim being absolute avoidance of BH.

### Basal insulin titration in CSII group

The basal insulin delivery rate will be titrated according to fasting, bedtime, pre-prandial and 4 am glucose levels ensuring absence of recurrent low glucose levels at these times (checkpoints). Increased or decreased delivery will be commenced from the previous basal insulin checkpoint level, i.e. if low at 4 am—decrease from bedtime; if high fasting increase from 4 am.

Mean fasting; bedtime; 4 am and pre-prandial blood glucose:

**Within target**: No change to basal delivery rate.

**Above target**: Increase basal insulin by 0.1 U/hr from previous check point.

**Below target or unexplained late post-prandial hypoglycaemia**: Decrease basal insulin by 0.1 U/hr from previous check point.

During periods of illness, basal insulin rates may need to be altered and this will be guided by SMBG levels.

### Meal-time insulin bolus in all groups (CSII and MDI)

Carbohydrate counting skills and bolus dose adjustment in light of current blood glucose level / individualised insulin carbohydrate ratios will be reviewed in all participants. Aspart or lispro will be delivered either by subcutaneous injection or as a subcutaneous pump bolus before all meals and snacks with substantial carbohydrate content.

Insulin: carbohydrate ratios will be calculated for all individuals using the ‘500 rule’ and using total daily insulin doses pre-randomisation. The ‘500 rule’ is:

500 divided by the TDD (Total Daily Dose of insulin) = grams of carbohydrate covered by one unit of aspart or lispro.

In the event of high pre-prandial glucose levels corrective doses will also be recommended with meals as part of the meal time bolus. This will be calculated using the ‘100 rule’ for estimation of Insulin Sensitivity Factor. The ‘100 rule’ is:

100 divided by the TDD (Total daily Dose of insulin) = glucose drop in mmol/l per 1 unit of aspart or lispro.

This will be presented to all participants as ‘*1 unit of aspart / lispro will reduce your blood glucose by x mmol/l*’.

Corrective doses with all pre-main meal boluses / prandial insulin injections will be encouraged according to the 100 rule when glucose level is above target.

The insulin: carbohydrate ratio and Insulin Sensitivity Factor for that period of the day will be adjusted accordingly in the event that:

The glucose level is consistently below or above target 2 h after a bolus / prandial insulin injection.

If any unexplained hypoglycaemic event occurs 2 h after a bolus / prandial insulin injection.

### Telephone contact

Participants will be contacted by telephone daily for the first week after starting the study intervention and thereafter weekly throughout the RCT to reinforce the primary goal of BH avoidance, provide clinical review / support, and ensure diary completion.

### Study follow up

Participants will attend for a study visit every four weeks during the RCT for collection of SMBG/hypoglycaemia diary and HbA1c. One week prior to each visit participants will have a blinded CGM device fitted and these data will be downloaded at the visit. Participants will have their weight measured at each follow up visit and this, along with details of insulin dosage, will be recorded on visit specific CRFs. Both investigator and participant will remain blinded to the results of the blinded CGM data during the RCT period. Clinical review at each follow up visit will reinforce the primary goal of BH avoidance. At each follow up visit information will be collected on any episodes of hypoglycaemia experienced, duration of RT-CGM monitoring usage and RT-CGM alarm settings.

At week 24, participants will attend for the primary RCT completion visit. This will include blinded CGMS data download, collection of SMBG/hypoglycaemia diary, and HbA1c. Participants will also be asked to complete the ‘end of RCT’ study-specific questionnaire booklets assessing hypoglycaemia experience and other PROs (Table 2).

On the same day, participants will be invited to attend for ‘end of RCT’ stepped hyperinsulinaemic hypoglycaemic clamp as described below.

At the end of this intervention period, participants will be asked to attend for repeat detailed cardiac autonomic function testing and subjective assessment of global autonomic symptoms.

### Post primary RCT follow-up

At the end of the 24-week RCT, participants will return to routine clinical care. Those randomised to CSII may stop this if they and their clinical team wish. Commencement of CSII according to NICE guidance [34] will be considered in those previously randomised to MDI. Those participants who were randomised to RT-CGM will continue with this intervention for a further 18 months constituting an overall 24 month RCT of RT-CGM augmented glucose monitoring vs SMBG alone. RT-CGM will not be offered to those not randomised to this intervention, as it is not currently recommended by NICE. All participants will be invited to attend three follow-up visits 6, 12 and 18 months post primary RCT (Table 1). Participants will be fitted with a blinded CGM device for 7 days before each follow-up visit. This visit will include collection of SMBG/hypoglycaemia diary; SMBG / CGM data download, HbA1c measurement. Participants will be required to complete questionnaire booklets (Table 2) at each follow-up visit.

The end of the study will be the last follow-up visit of the last participant scheduled for 24 months after the commencement of study interventions.

### Hypoglycaemic clamp study

A stepped hyperinsulinaemic hypoglycaemic clamp study [49] will be conducted in participants who are willing to undergo this procedure for which separate informed consent will be obtained. It is envisaged that approximately 25% of participants will be studied. Additional exclusion criteria will be in place to ensure participant safety:

Age >60 years.

History of epilepsy (seizures not primarily induced by hypoglycaemia).

Known ischaemic heart disease.

Other significant disease which in the judgement of the investigator precludes participation.

Participants will be fitted with a retrospective CGM sensor to be worn typically for five to seven days (at least 24 h) preceding the study day. This will be downloaded on the morning of the study to determine whether any antecedent biochemical hypoglycaemia (BH) occurred over the 24 h period prior to the clamp. Studies will be postponed to another day if any CGM and/or self-monitored capillary glucose below 3.0 mmol/l are detected during the preceding 24 h. For participants who required rescheduling, a further 72 h of CGM will be organised. All participants will be advised to fast from 22:00 h and to avoid caffeine for 24 h before the study.

The participant will be admitted to the clinical research facility at 7 am on the day of the study. On arrival, an intravenous cannula will be inserted in the ante-cubital vein of the non-dominant arm and blood glucose will be stabilized using sliding scale insulin infusion aiming initially for blood glucose 6.0–7.0 mmol/l and then 5.0–6.0 mmol/l between 10.30 am and 11 am for clamp initiation.

A second retrograde cannula will be inserted into a vein on the dorsum of the non-dominant hand for the sampling of arterialised venous blood. The hand will be kept in a purpose-built heated box (Temp 50–60°Celsius) before inserting the retrograde cannula and throughout the clamp study. A slow intravenous infusion of saline will be used as needed to keep the sampling line patent. During this period of stabilization, participants will be shown how to perform specific cognitive function tests (Four choice reaction time [50-52] and Stroop tests [53,54]) and asked to practise the tests until they achieve consistent results (typically 5 practice sessions). Four-choice reaction time is a test of attention, discrimination and motor speed reaction while Stroop tests are a group of related sub-tests all requiring selective attention and mental tracking.

At the start of the clamp a primed infusion of 60 mU/m^2^/min soluble human Actrapid insulin will be started via the non-dominant antecubital vein catheter. Dextrose infusion rates will be adjusted as needed, aiming to stabilise plasma glucose at 5.0 mmol/l at 40mins followed by step-wise lowering to 3.8 mmol/l, 3.4 mmol/l 2.8 mmol/l and 2.4 mmol/l. Each step will last 40 min allowing 20 min to achieve new target and 20 min for stabilization at that level. Samples for plasma glucose will be obtained every 5 min and analysed in real-time but participants will be blinded to these glucose levels throughout the study.

At the end of each clamp stage participants will be asked to complete a validated symptom questionnaire [55,56] followed by the four choice reaction time test and Stroop test. Each symptom will be graded on a visual analogue scale from 1 (not at all) to 7 (very severe).

Arterialised venous blood samples for insulin, catecholamines, growth hormones, glucagon and cortisol will be obtained every 10 min during the first 40 min of the study (euglycaemia) followed by every 20 min during progressive hypoglycaemia. Heart rate and blood pressure will be recorded every 20 min. In addition, spectral analysis of heart rate variability and assessment of cardiac vagal baroreflex sensitivity (BRS) will be carried out during each clamp stage. At the end of the study, insulin infusion will be reduced to basal insulin requirements and dextrose infusion increased to raise blood glucose to euglycaemia. Participants will be provided with lunch with post-meal insulin bolus and re-established on their usual insulin regimen thereafter.

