### Trial intervention and study procedures

Schedule for study visits is given in Table 1.

**Table 1 T1:** Visit schedule

**Study period**	**4 week wash in period**						**24 week primary RCT**															**18 month RT-CGM RCT continuation**					
**Visit number**	**1**	**2**	**3**	**4**	**5**	**6**	**7**	**8**	**9**	**10**	**11**	**12**	**13**	**14**	**15**	**16**	**17**	**18**	**19**	**20**	**21**	**22**	**23**	**24**	**25**	**26**	**27**
informed consent	x																										
eligibility criteria	x																										
given information sheet on clamp study	x																		x								
hypoglycaemia screening questionnaire	x		x																								
HbA1c	x		x							x		x		x		x		x		x			x		x		x
C-peptide and plasma glucose	x																										
retinal photographs		x																									
urine albumin:creatinine ratio		x																									
demographic info			x																								
concomitant medication			x							x		x		x		x		x		x			x		x		x
full physical examination			x																	x							
history of glycaemic control										x		x		x		x		x									
full medical history including glycaemic control			x																	x			x		x		x
vital signs			x							x		x		x		x		x		x			x		x		x
height			x																								
weight			x							x		x		x		x		x		x			x		x		x
TFTs					x																						
Coeliac antibody					x																						
short synacthen test					x																						
detailed SH history			x							x		x		x		x		x		x			x		x		x
Modified Clarke/Edinburgh			x																	x			x		x		x
QoL questionnaires			x																	x			x		x		x
week 4 short questionnaire pack										x																	
4 week Blood Glucose / hypo diary	x		x							x		x		x		x		x		x							
7 day CGMS placement		x							x		x		x		x		x		x			x		x		x	
Autonomic function tests				x																	x						
clamp study			x																x								
education programme						x																					
Insulin administration education session							x																				
Home glucose monitoring/RT education session								x																			

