# designed by [name], [name] and [name] (King’s College London).

#### Baseline hypoglycaemic clamp study

A stepped hyperinsulinaemic hypoglycaemic clamp study will be conducted at baseline and at 24 weeks with participants who are willing to undergo this procedure for which specific consent will be sought separately. It is envisaged that approximately 25% of participants will be studied. The method is described in detail later.

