#### Autonomic function testing

Before the start of the RCT, participants will attend for non-invasive detailed cardiac autonomic function testing using the recommendations in the review by Tesfaye et al. [46]. These will include heart rate response to deep breathing, a Valsalva maneuver and heart rate and blood pressure response to standing interpreted using age normative values. Spectral analysis of heart rate variability and assessment of cardiac vagal baroreflex sensitivity (BRS) will be carried out over a five minute period of controlled breathing. Structured assessment of global autonomic function will be made using the Autonomic Symptom Profile Questionnaire [47].

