#### Concomitant autoimmune disease screening

Participants will attend for a short synacthen test to screen for adrenocortical insufficiency. At this visit a sample will also be taken for serum thyroid stimulating hormone assay to exclude thyroid disease and for anti-endomysial antibody analysis to exclude coeliac disease. New diagnoses of other autoimmune diseases will not preclude participation in the study. If indicated participants with newly diagnosed autoimmune disease will be referred to an appropriate specialist for further investigation and management.

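### Table 1 schedules the baseline clamp (visit 3) before the trial's own adrenal screen (visit 5), so clamp eligibility is judged without that result

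*Protocol article*

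**What the plan says.** The section on the baseline clamp states: "A stepped hyperinsulinaemic hypoglycaemic clamp study will be conducted at baseline and at 24 weeks". Taking part is voluntary, has its own consent and is expected to involve about a quarter of participants.

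The section headed Hypoglycaemic clamp study introduces its list with "Additional exclusion criteria will be in place to ensure participant safety". The list covers age over 60, epilepsy, known ischaemic heart disease, and finally "Other significant disease which in the judgement of the investigator precludes participation". The clamp then lowers plasma glucose in steps to 2.4 mmol/l and samples cortisol and catecholamines, among other hormones.

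The section on concomitant autoimmune disease says "Participants will attend for a short synacthen test to screen for adrenocortical insufficiency". It adds "New diagnoses of other autoimmune diseases will not preclude participation in the study", with specialist referral where indicated.

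Table 1 has separate rows for the clamp, for "Autonomic function tests" and for "short synacthen test", each marked against numbered visits.

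**The concern.** The clamp has its own exclusions, justified by safety. One of them is open-ended and depends on what the investigator knows about the participant's health that day. The trial orders a test for adrenocortical insufficiency, a condition that bears on the response to induced hypoglycaemia. If that test comes two visits after the clamp, the judgement is made without a result the trial is about to have anyway.

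The same exclusion is also applied with different information at the two clamps: without the adrenal result at baseline and with it at 24 weeks. Someone found to have adrenal disease at visit 5 could drop out of the second clamp, which loses a pair after the baseline exposure. Alternatively, that person could be managed and clamped again, so that the change in cortisol and related responses partly reflects the management.

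**Working it through.** **Visit order.** Reading each Table 1 row by column position gives:

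| Procedure | Visits |
|---|---|
| Sensor placement (first) | 2 |
| Full history and physical examination (baseline) | 3 |
| Clamp | 3 and 19 |
| Autonomic function tests | 4 and 21 |
| Short synacthen test | 5 only |
| Education programme | 6 |

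Visits 1 to 6 all sit under the wash-in heading. The adrenal screen is thus planned before the randomised period but after the baseline clamp.

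**Against the text.** The methods describe the clamp, the autonomic tests and the autoimmune screen in that order but never state a sequence. The only timing given for the autonomic tests is "Before the start of the RCT, participants will attend for non-invasive detailed cardiac autonomic function testing". Nothing in the text places the adrenal test ahead of the clamp, so the order rests on Table 1 and on visits running in number order.

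**Against the exclusions.** None of the four clamp exclusions names an adrenal or autonomic result. Only the investigator's judgement on other significant disease could use one.

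**Exposure.** Expected clamp sample: 0.25 × 100 = 25. The targets below the 5.0 mmol/l stage are 3.8, 3.4, 2.8 and 2.4 mmol/l, at 40 min each: 4 × 40 = 160 min in all, of which 2 × 40 = 80 min belong to the steps at 2.8 or lower. Each step includes 20 min of transition.

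**Leverage of one case.** One person is 1/25 = 4% of the sample. If management between clamps shifts that person's change by d, the mean paired change over 25 shifts by d/25 = 0.04d.

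**Frequency.** The documents give none. As a pure assumption, with prevalence p of undiagnosed adrenal insufficiency the chance that at least one of 25 is affected is 1 − (1 − p)^25. For p = 0.5% this is 1 − 0.995^25 = 11.8%; for p = 2% it is 1 − 0.98^25 = 39.7%. These figures make no allowance for what history and examination at visit 3 would already reveal, and the conclusion does not rest on them.

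**Week-24 clamp.** Table 1 marks it at visit 19, a sensor-placement visit. The section on study follow-up puts it on the day of the RCT completion visit, which by its contents (HbA1c, questionnaires, full examination) appears to be visit 20. The two do not agree.

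**The case against.** Much of the opposing case stands.

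- **No rule is broken.** The listed exclusions do not call for a synacthen result. Full history and examination fall at visit 3, so the judgement has a basis. A reader might infer that the protocol contradicts itself. It does not: the screen is simply not linked to clamp eligibility.
- **New autoimmune diagnoses do not bar participation.** True, but that sentence concerns the main study. The clamp has separate consent and additional exclusions, so it does not settle the matter.
- **Autonomic tests.** A reader might extend the point to these, since they also follow the baseline clamp. The documents do not support that. They are an assessment repeated at the end of the intervention, and they follow the clamp at both timepoints (visits 3 then 4, 19 then 21). Severe neuropathy is to be identified from clinical history, and it is a hypothesised reason for non-response that the trial sets out to study.
- **Confounding.** A reader might infer that the order confounds baseline clamp responses. It does not: pre-existing disease affects a baseline clamp whichever test comes first. The adrenal result is due before the randomised period, so its consequences are balanced in expectation between CSII and MDI and between RT-CGM and none.
- **Monitoring.** Glucose is measured every 5 min in real time with adjustable dextrose, and heart rate and blood pressure every 20 min. This lessens the safety concern but does not supply the missing result.
- **Condensed article.** The full protocol may describe how clamp eligibility is checked. The visit order, however, is stated here and is open to comment.
- **Weak evidence of order.** The mismatch at week 24 shows that the clamp row may not be exact. This lowers confidence and is itself a reason to correct the table.

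**Conclusion.** The point holds for the adrenal screen alone. As scheduled in Table 1, the baseline clamp precedes the synacthen test, and the safety judgement on other significant disease is made without it. The main exposure is safety at the baseline clamp for about 25 people. The validity exposure is small: the paired baseline-to-24-week hormone change and the non-randomised comparison of responders with non-responders, and only if someone is newly diagnosed and managed between clamps. One such person would be 4% of the subset. The frequency cannot be derived from the documents. The primary outcome and the randomised clamp comparisons are not affected.

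Confidence is moderate. The reading assumes that visits run in number order and that the clamp row of Table 1 is correct at baseline, although it fits the text poorly at week 24.

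**What to change.** Reconcile the visit order in Table 1 with the safety purpose of the clamp exclusions, so that for clamp participants the synacthen result is on file when clamp eligibility is judged. One way is to bring that sample forward to an earlier wash-in visit. Which results preclude a clamp stays with the investigators and sponsor.

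Leave the baseline clamp, the sensor period before it and the autonomic tests where they are. This keeps the clamp-then-autonomic order the same at both timepoints and avoids a further sensor period.

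In the clamp analysis, flag anyone newly treated between the two clamps. Reconcile the week-24 clamp visit between Table 1 and the follow-up section.

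The cost is one sample and its result needed earlier for about 25 people, plus an edit to the table. No new test is required.
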